#### Definition of covariates

Potentially associated factors of frailty in the models included [16, 36–43] age, sex, ethnicity, education level, marital status, body mass index (BMI), living alone, living conditions, smoking, alcohol consumption, falling accidents in the past 12 months, immobilization for more than 4 weeks, polypharmacy, fatigue, resistance (ability to climb stairs), ambulation (ability to walk 100 m), illnesses (> 5), loss of more than 5 % body weight, nutritional risk, ADL, instrumental ADL, depression, cognitive function, handgrip strength, vision, hearing, sleeping, urinary function, and defecation function.

Age was grouped as 65–74 years old, 75–85 years old, and 85 years old and above. Ethnicity was categorized as Han and ethnic minorities. Education level was categorized as illiterate, primary school, junior high school, and high school and above. Marital status was categorized as married and divorced or widowed. Living alone was categorized as living alone or not living alone [40]. Living conditions was classified as living in a building with an elevator, a building without an elevator, or a bungalow. Polypharmacy was categorized as 0, 1–2, 3–4, 5–6, and more than 7 [16].

BMI was calculated as body weight divided by height (in meters) squared (kg/m^2^) [18] and was used to classify patients into groups of < 19 kg/m^2^, 19 to < 21 kg/m^2^, 21 to < 23 kg/m^2^, and ≥ 23 kg/m^2^. Participants’ weight in kg was measured to the nearest 0.1 kg using a digital electronic chair scale, and height (in cm) was measured to the nearest 1 mm using a stadiometer. Study participants were weighed while wearing light clothing and no shoes.

We referred to the FRAIL scale [38, 44], such as the items of fatigue, resistance (ability to climb stairs), ambulation (ability to walk 100 m), illnesses (> 5), and loss of more than 5 % body weight, which has been validated in Chinese older adults [45].

Nutritional risk was measured using the MNA-SF, a six-item scale with scores ranging from 0 to 14 points [19]. Patients were categorized into patients at risk of malnutrition (8–11 points) or malnourished (0–7 points) [39]. The MNA-SF has been validated in the Chinese population and has excellent test characteristics [10, 46].

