#### Procedure

After obtaining participants’ informed consent, an inventory will be made of possible confounders. This includes the following: sociodemographic data (age, sex, ethnicity, marital status, education level, type of insurance), hospital admissions, medical diagnosis, living conditions, smoking, and alcohol consumption.

Anthropometric indicators will include admission to the following. (1) Standing height; in the case of bedridden patients, the formula of Chumlea will be used to estimate height [61]. (2) Weight. (3) BMI. (4) Handgrip strength in kg, measured with a hydraulic hand dynamometer (EH101; Camry, Guangdong Province, China)  [62]. Patients will be seated with forearms resting on the arms of a chair and asked to perform three maximum force trials with their dominant hand, using the second handle position. The maximum grip score among the three values will be used [63]. Nutritional risk will be measured using MNA-SF score (0–11 points ranging from “malnourished” to “at risk of malnutrition”) [10]. For frailty assessment, the Fried frailty phenotypes (FPs) [22] will be adopted as the “standard” for comparisons with the frailty model developed in the first stage of the current study. The five phenotypes of frailty that will be used include poor appetite, exhaustion, low physical activity, poor walking ability, and poor twisting ability of fingers. Participants are to be classified as non-frail, pre-frail, and frail when meeting 0, 1 or 2, and ≥ 3 criteria [43].

To determine the degree of dependency, the BI will be used to perform physical function assessment (basic ADL) among patients. Data collection will be carried out by direct observation or by asking the patient, if possible. Scores range from 0 to 100, with a higher score indicating greater independence.

Biochemical markers include serum albumin and prealbumin (colorimetry), hemoglobin and hematocrit (fluorescence and optical methods), cholesterol (enzymatic techniques), and myokines (enzyme-linked immunosorbent assay (ELISA); Shanghai Enzyme-Linked Biotechnology Co., Ltd.).

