#### Statistical analysis

Continuous variables are described using mean and SD or median with interquartile range in the case of a skewed distribution. Categorical variables are described as number and percentage. ANOVA will be used to examine the statistical differences in variables among different groups. We will perform bivariate analyses using the χ^2^ test or Fisher’s exact test for qualitative variables and Kruskal–Wallis test for quantitative variables. Cox proportional hazards models will be constructed to determine the association of frailty score at baseline with mortality. Multiple linear regression models will be applied to evaluate the relationship between baseline frailty score and health clinical outcomes. We will use the Kappa statistic to evaluate the consistency of the new frailty prediction model and FP. The correlation between biochemical markers and frailty will be assessed using Pearson’s correlation coefficient. All statistical analysis will be performed using Stata version 14 for Windows (Stata Corp, College Station, TX, USA). A *P* value of less than 0.05 is considered statistically significant.

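### The only analysis named for the biochemical markers is a crude correlation with frailty, although age and sex are collected as possible confounders; an adjusted estimate should be added (minor)

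*Protocol article*

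**What the plan says.** All places are in the protocol article.

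- **Markers** (second stage, Procedure): "Biochemical markers include serum albumin and prealbumin (colorimetry), hemoglobin and hematocrit (fluorescence and optical methods"), followed by cholesterol and myokines.
- **Marker analysis** (second stage, Statistical analysis): "The correlation between biochemical markers and frailty will be assessed using" Pearson's correlation coefficient. No covariate, stratum or partial correlation is named. The significance threshold for the section is P<0.05.
- **Other models in the same section**: Cox regression relates baseline frailty score to mortality, and multiple linear regression relates it to clinical outcomes. Neither is said to involve the markers.
- **Confounders** (second stage, Procedure): "an inventory will be made of possible confounders", and the list opens with "sociodemographic data (age, sex, ethnicity, marital status, education level, type of insurance").
- **Link of age and sex to frailty**: the Background calls frailty an age-related condition. The first-stage list of potentially associated factors (Definition of covariates) begins "age, sex, ethnicity, education level, marital status, body mass index (BMI").
- **Form of the frailty variable** (second stage, Procedure): "Participants are to be classified as non-frail, pre-frail, and frail", by number of criteria met.

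**The concern.** The protocol treats age and sex as possible confounders and as factors related to frailty, and it collects both. The one analysis it assigns to the markers cannot use them, because a Pearson coefficient is a pairwise statistic that pools men and women of all ages.

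If a marker also differs by age or sex, it will correlate with frailty in the pooled sample even when the two are unrelated among patients of the same age and sex. Hemoglobin and hematocrit are the most plausible cases, since both are generally lower in women. That is general knowledge and not a statement in the protocol.

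At stake is interpretation. Each marker can be reported as significantly correlated with frailty, and a reader could not tell a marker signal from an age or sex difference. Switching from Pearson to a rank coefficient would not solve this, because either is open to confounding when crude.

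**Working it through.** **Plan's own figure.** There is none to reproduce: the article gives no sample size, power or target coefficient for the marker correlation. The second-stage 266 was set for readmission. The Abstract and the limitations give 266 as the total, while the sample size section speaks of two groups of 266. I use 266 and show 213 (266 × 0.8 = 212.8, after the 20% refusal allowance) and 532 (2 × 266) as alternatives.

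**Formula.** Suppose marker and frailty are unrelated given a confounder C. The crude coefficient is then

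r = r(marker, C) × r(frailty, C).

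With d = atanh(r) × √(N − 3), the chance of two-sided P<0.05 is Φ(d − 1.96) + Φ(−d − 1.96). At N=266 the smallest significant |r| is 1.96/√(264 + 1.96²) = 0.120.

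**One confounder, N=266.** All correlations are assumptions; signs are omitted.

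| r(marker, C) | r(frailty, C) | Induced r | Chance of P<0.05 |
|---|---|---|---|
| 0.1 | 0.1 | 0.01 | 5% |
| 0.2 | 0.2 | 0.04 | 10% |
| 0.4 | 0.1 | 0.04 | 10% |
| 0.4 | 0.2 | 0.08 | 26% |
| 0.3 | 0.3 | 0.09 | 31% |
| 0.4 | 0.3 | 0.12 | 50% |
| 0.4 | 0.4 | 0.16 | 74% |

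Worked line: for r=0.08, d = 0.0802 × √263 = 1.30, so Φ(−0.66) + Φ(−3.26) = 0.255.

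**Sex alone, as differences in SD.** Assume half the sample are women. A difference of δ within-sex SD corresponds to a correlation of δ/√(δ² + 4).

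- Marker 0.75 SD, frailty score 0.3 SD: 0.351 × 0.148 = 0.052, about 13.5%.
- Marker 0.75 SD, frailty score 0.5 SD: 0.351 × 0.243 = 0.085, about 28%.
- Marker 0.5 SD, frailty score 0.2 SD: 0.243 × 0.100 = 0.024, about 7%.

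In simulation of these three cases (20,000 replicates), the sex-adjusted partial correlation was significant in 4.9% to 5.1% of replicates.

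**Age and sex together** (taken as uncorrelated with each other, N=266).

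- Same direction: 0.4 × 0.1 + 0.2 × 0.3 = 0.10, 37%.
- Opposite directions: 0.2 × 0.3 − 0.4 × 0.1 = 0.02, 6%.

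**Sample size.** The induced correlation does not shrink with more patients. For r=0.08 the chance is 21% at N=213, 26% at 266 and 45% at 532.

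**Cost of adjustment.** Two covariates reduce the degrees of freedom from 264 to 262. The smallest significant |r| becomes 1.96/√(262 + 1.96²) = 0.120, unchanged to three decimals.

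**The case against.** The strongest reply is that the protocol plans a correlation and claims nothing causal. If marker and frailty both vary with age, their marginal correlation really is non-zero, and detecting it is no error for that quantity. This stands. The percentages above are error rates only if the question is association within age and sex. The protocol's own label of possible confounders is the reason to answer that question as well.

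A reader might infer that spurious links are likely. The documents do not support that. They give no correlation of age or sex with any marker or with the frailty score. The sex argument is made only for hemoglobin and hematocrit, not for albumin, prealbumin, cholesterol or myokines. Age and sex effects can partly cancel. The entry criteria (age 65 or more, Barthel Index of at least 75, and FRAIL 0 to 2 carried over from the first stage) may also weaken the relations with baseline frailty.

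A reader might also infer that confounded markers would be named as intervention targets. The text does not say so: in the Abstract and Background, intervention target information is tied to applying the early warning model, and the markers do not appear under Outcome parameters.

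It can also be said that a condensed article leaves covariates to a fuller plan; it lists none for its regression models either. That lowers the weight. It does not remove the point, because here the article commits to an estimator that has no place for covariates. Finally, the general ANOVA and Kruskal–Wallis comparisons might cover the markers too, so the correlation is the only analysis named specifically for them rather than certainly the only one. Those comparisons are also unadjusted.

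**Conclusion.** The point holds at minor weight. The analysis named for markers and frailty is unadjusted, while the same protocol collects age and sex as possible confounders and links both to frailty. Crude associations may therefore partly reflect age or sex.

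How much cannot be fixed from the documents. At n=266 and with no association within age and sex, the chance of a significant crude correlation runs from about 5% to 50% or more, depending entirely on assumed correlations. The return to about 5% after adjustment assumes that age and sex are the only confounders. The finding is that confounding is possible and cheap to address, not that it is shown or probable. It concerns an ancillary analysis and leaves the primary and main secondary endpoints untouched.

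**What to change.** In the second-stage Statistical analysis section, add an age- and sex-adjusted estimate for each marker: either a partial rank correlation, or a regression of the frailty score on the marker with sex and continuous age as covariates. State that any claim of a marker-frailty association rests on this estimate, and that the crude coefficient is reported as descriptive. The rank form also suits a frailty variable recorded in three ordered classes.

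The cost is one or two sentences and two degrees of freedom. No new data are needed, since age and sex are already collected.

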#### Organization and quality control

The data will be gathered by the primary investigator and research assistants. The primary investigator is responsible for the informed consent procedure, final participant selection, measurements, analysis, and reports. The primary investigator will be assisted by two research assistants. Data flow will be controlled by the primary investigator. Data entry and control will be conducted by the research assistants under supervision of the investigator. The primary investigator is responsible for the data cleaning and analysis.

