### Applying the frailty prediction model in the clinic

#### Population and inclusion and exclusion criteria

All older patients (age 65 years or more, BI scores ≥ 75 points, and estimated survival time > 3 months) who were hospitalized for minimum of 4 days in the wards of Peking Union Medical College Hospital, will be screened by a research assistant using the frailty prediction model. The other inclusion criteria are the same as in the first stage of the study. In the second stage, we will also exclude patients who were included in model development during the first stage.

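### Stage 2 describes no separation between the staff who compute the model score and those who rate the Fried standard and the day-30 Barthel and frailty outcomes

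*Protocol article*

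**What the plan says.** All of this is in the second-stage part of the protocol article, under Applying the frailty prediction model in the clinic.

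- **Scoring.** Under Population and inclusion and exclusion criteria, older inpatients "will be screened by a research assistant using the frailty prediction model".
- **Staffing.** The section Organization and quality control gives the collection of data to the investigator and the assistants jointly. It then names one person, the investigator, as "responsible for the informed consent procedure, final participant selection, measurements, analysis, and reports"; the same person also controls the data flow and cleans the data. On the size of the team it says: "The primary investigator will be assisted by two research assistants". The assistants have a further duty, described in these words: "Data entry and control will be conducted by the research assistants under supervision of the investigator".
- **Reference standard.** Under Procedure, the Fried phenotype serves as the standard "for comparisons with the frailty model developed in the first stage of the current study". The agreement analysis is given under Statistical analysis: "We will use the Kappa statistic to evaluate the consistency of the new frailty prediction model and FP".
- **Barthel Index.** Under Procedure: "Data collection will be carried out by direct observation or by asking the patient, if possible".
- **Primary composite.** Under Outcome parameters, the 30-day composite includes frailty and a Barthel decline of at least 10 % from admission. It also includes death, ICU admission, non-elective readmission and major complications with an adjudicated diagnosis. No rater is named for any day-30 outcome, and no adjudicator for the complications.

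**The concern.** The same three people, as far as the article shows, produce the index result, select the patients, take the measurements, enter the data and analyse them. Nothing described keeps the model result from the person who rates the measures it is compared with.

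Two analyses are exposed. The first is kappa between model and Fried phenotype. The listed Fried criteria of poor appetite, exhaustion, low activity and poor walking ability rest on patient report or rater judgement. A rater who knows that the model says high risk may resolve doubtful items towards agreement. The second is the association between the score and the composite, through day-30 Barthel decline and day-30 frailty. Once ratings have been collected with knowledge of the score, no analysis can remove the effect, so it has to be prevented in the conduct of the study.

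**Working it through.** **1. Who can know the score, and when.** The article states no figure that depends on masking, so there is nothing to reproduce. The check is to set the sections side by side.

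| Measure | Needs rater judgement? | Must it follow the score? |
|---|---|---|
| Admission Barthel | Yes | No: a score of at least 75 is an entry criterion, and ADL by Barthel is a candidate predictor |
| Fried phenotype (kappa) | Yes, for most criteria | Order not stated |
| Day-30 Barthel, day-30 frailty | Yes | Yes: the score is produced at screening |
| Readmission, ICU admission | Less; calling a readmission non-elective needs some judgement | Yes |
| Major complications | Called adjudicated; masking not described | Yes |
| Death | Hardly | Yes |

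The exposure is therefore certain in time only for the day-30 measures, and possible for the Fried rating.

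**2. How small a rating shift makes a primary event.** Entry requires a Barthel score of 75 to 100. A 10 % decline is 0.10 × 75 = 7.5 points to 0.10 × 100 = 10 points. If items move in 5-point steps (assumption; the article does not give the step), both need a 10-point fall, which is two one-step shifts.

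**3. Illustration for the composite.** Suppose there is no true difference, the event rate is p in both score groups, and knowledge of the score turns a share s of non-events into events in the high-score group only. Then RR = [p + (1 − p)s] / p. The values of s are assumed. The value 17 % is the readmission rate in the second-stage sample-size section. The values 26.5 %, 40 % and 54 % are the frailty figures in the first-stage sample-size section, used here as assumed composite rates.

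| p | s = 5 % | s = 10 % |
|---|---|---|
| 17 % | 0.2115 / 0.17 = 1.24 | 0.253 / 0.17 = 1.49 |
| 26.5 % | 0.30175 / 0.265 = 1.14 | 0.3385 / 0.265 = 1.28 |
| 40 % | 0.43 / 0.40 = 1.075 (about 1.08) | 0.46 / 0.40 = 1.15 |
| 54 % | 0.563 / 0.54 = 1.04 | 0.586 / 0.54 = 1.09 |

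**4. Illustration for kappa.** Take frail versus not frail, Fried prevalence 40 %, and model sensitivity and specificity of 0.75 (all assumed).

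- Cells: both positive 0.30, model only 0.15, Fried only 0.10, both negative 0.45. Observed agreement is 0.75. Chance agreement is 0.45 × 0.40 + 0.55 × 0.60 = 0.51. Kappa = (0.75 − 0.51) / (1 − 0.51) = 0.49.
- Move 10 % of the discordant Fried ratings into agreement: observed 0.775, chance 0.45 × 0.405 + 0.55 × 0.595 = 0.5095, kappa = 0.2655 / 0.4905 = 0.54.
- At 20 % and 30 % moved, kappa is 0.59 and 0.64.

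Over prevalences of 26.5-54 % and sensitivity and specificity of 0.75-0.80, each 10 % of discordant ratings moved adds about 0.04-0.06 to kappa. Stage-2 entry carries over the stage-1 requirement of no frailty on the FRAIL scale, so the true Fried prevalence may be lower than these values.

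**The case against.** The strongest reply is that this is a condensed article. Form access and masking are operational details that a full protocol may hold. Being responsible for measurements can mean accountability rather than rating each patient. It is also an inference that the screening assistant is one of the two named later. This stands in part: the article does not say that raters see the score, and a reader who infers that outcome assessment is known to be unmasked goes too far. However, the article does set out its staffing and quality control, and that stated arrangement gives overlapping access to one small team. If a separation exists elsewhere, one sentence settles the point.

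Three stronger readings are tempting and are not supported:

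- **That the score precedes every rating.** Admission Barthel is needed for eligibility and perhaps for the score itself, and the timing of the Fried rating is not given.
- **That the relative risk would be distorted to 1.24-1.49.** Those values use 17 %, which the article gives as a readmission rate. The composite also contains frailty and other events, so its rate may be much higher and the distortion smaller.
- **That every error must favour the model.** The model is meant to supply targets for intervention. If staff act on a high score, events in that group could fall and the association could weaken. The upward tendency is clearer for kappa than for the composite.

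A simple split of tasks also has its own weakness. If one assistant rates Barthel at admission and the other at day 30, differences between raters could create or hide a 10-point decline.

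**Conclusion.** The point holds in limited form. As described, nothing keeps the raters of the Fried standard, or of day-30 Barthel and frailty, from knowing the model result. Kappa would tend to be inflated, and the score-outcome association may be. Death is little affected, so the planned Cox model for mortality is largely safe from this problem. Complications are called adjudicated, though by whom and with what information is not said.

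The size of the bias cannot be derived from the documents. The relative risks of about 1.08-1.15 (40 % composite rate) and 1.24-1.49 (17 %), and the kappa gain of 0.04-0.06 per 10 % of discordant ratings moved, all rest on assumed shifts and rates. They show scale only. This is an inexpensive improvement worth making before recruitment, not a defect that invalidates the study.

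**What to change.** State in the protocol who scores, who rates, and what each can see:

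1. Record the admission Fried and Barthel ratings before the score is computed, or without access to it.
2. One existing assistant computes the score and locks it in the database. If ADL is retained in the model, this assistant takes over the admission Barthel value already recorded.
3. The other assistant, without access to the score, rates the Fried criteria and the Barthel Index at both admission and day 30, and day-30 frailty. Using the same rater at both times keeps change from being mixed with rater differences.
4. Data-entry rights follow the same split, because the assistants also enter and check the data.
5. Whoever adjudicates complications and non-elective readmission works from records that do not show the score. This should not all fall to the rating assistant.
6. The score may still go to treating clinicians; the masking concerns raters and adjudicators only.

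The cost is task allocation and database access rights, with no added visits or sample size. The downside is less flexible scheduling, since each assistant is tied to one role and the rating assistant to both time points.
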